**Figure 2 fig2:**
[figure not shown]
Sample size formula.

Therefore, for each of the intervention and control groups, 102 students will be randomly selected from among the second-high school students of Ramhormoz city (including 30% chance of dropping out). We try to select the number of people in each grade equally.

### Ethics approval and consent to participate

#### Recruitment and consent

Ethical approval for the study was granted by the Ethics Committee of Tehran University of Medical Sciences (Approval date: 27/05/2023, Reference: IR.TUMS.SPH.REC.1402.075). This study aimed to assess the impact of a social media-based educational intervention on mental health literacy. Both participants and their parents were informed that participation was entirely voluntary, their data would remain confidential, and findings would only be presented in aggregate form for research purposes.

#### Consent and assent collection process

##### To ensure ethical rigor and avoid potential coercion

*Parental Consent:* Consent was obtained electronically through an online form sent via parents’ mobile numbers provided by the school. Parents reviewed the study details and acknowledged their consent by clicking “agree.”*Adolescent Assent:* After parental consent was granted, adolescents were presented with a separate assent form within the online interface. They were individually informed about the study’s objectives, procedures, and voluntary nature in a private virtual setting. Adolescents had the opportunity to review and decide independently whether to participate by selecting “agree.”

#### Informed consent and protections

Detailed information about the study objectives, expected procedures, potential risks and benefits, confidentiality measures, and the voluntary nature of participation was provided to both participants and their parents or guardians.

#### Withdrawal option

Both participants and their parents were informed that they could withdraw from the study at any time without any penalties or negative consequences.

This dual-step consent and assent process was designed to uphold ethical standards and ensure that both parents and adolescents made fully informed, independent decisions.

#### Data protection

To ensure participant privacy and confidentiality, all collected data will be anonymized and securely stored.

#### Compensation for human subjects research

As a token of appreciation for their time and participation, participants will receive compensation in the form of a 10 GB internet package for 1 month.

#### Dissemination of results

Study results will be shared with the scientific community through publications and presentations, contributing to the broader understanding of mental health literacy interventions.

#### Inclusion/exclusion criteria

##### Inclusion criteria

To be eligible for this study, male students enrolled in public high schools in Ramhormoz city must meet the following criteria:

Have access to a smartphone with an internet connection.Demonstrate an understanding of both written and spoken Persian language.Express willingness to participate in the research and provide informed consent.Not having any known mental disorders or depressive symptoms.

#### Exclusion criteria

Participants will be excluded from the analysis if they:

Withdraw their consent or express unwillingness to continue the research at any stage.Migrate to another city or school during the study period.

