### Statistical analysis

The statistical analysis of this study will be based on the intention-to-treat (ITT) principle, which includes all randomized participants regardless of their adherence to the intervention or their status at the end of the trial. The ITT analysis will preserve the balance of baseline characteristics achieved by randomization and reduce the risk of bias due to selective reporting or loss to follow-up (Hemming et al., 2020).

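### The exclusion criteria and the intention-to-treat statement define two incompatible analysis populations

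*Protocol article*

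**What the plan says.** Under Exclusion criteria, the protocol article writes "Participants will be excluded from the analysis if they" and lists two triggers: "Withdraw their consent or express unwillingness to continue the research at any stage" and "Migrate to another city or school during the study period".

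The Statistical analysis section adopts ITT, an analysis "which includes all randomized participants regardless of their adherence to the intervention or their status at the end of the trial". Among its reasons it gives that ITT will "reduce the risk of bias due to selective reporting or loss to follow-up".

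Under Sample size calculation, the text below Figure 2 states that "for each of the intervention and control groups, 102 students will be randomly selected", a number described as "including 30% chance of dropping out".

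Other parts of the article bear on the point:

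- **Sampling method:** whole schools are allocated, three to each arm.
- **Method/design:** the trial has no blinding.
- **Data collection:** the questionnaire is an online link sent to students' phones, at baseline and at 3 and 6 months.
- **Incentives and participant engagement:** retention is named as a concern, with the control arm singled out.

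**The concern.** Both triggers can occur after a student's school has been allocated, and the wording removes him from the analysis, not merely from enrolment. A student who becomes unwilling or changes school is therefore out under one section and in under the other.

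If the exclusion rule is applied, the groups compared are no longer those formed by randomisation. They are the students who stayed willing and stayed put. Whether a student stays willing may depend on his arm: one arm is offered 15 sessions of 30 to 60 minutes over a month, the other a guide book at the end of the study, and everyone knows which is which. Read literally, a student who gave baseline and 3-month scores and then declined the 6-month questionnaire would lose all his data.

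If neither section is given priority, the analyst could choose between the two populations after seeing the results.

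**Working it through.** **1. The two rules side by side**

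| Student, after his school is allocated | Exclusion criteria | Statistical analysis (ITT) |
|---|---|---|
| Says he no longer wishes to continue | Out | In |
| Changes city or school | Out | In |
| Withdraws consent to use of his data | Out | Removal is legitimate |
| Does not answer one questionnaire link | Not mentioned | In, with a missing score |

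The first two rows are a direct contradiction. The article does not limit the exclusion rule to a per-protocol or sensitivity set. For the student who moves there is also no measurement reason to exclude him: the link reaches his phone wherever he lives, and his arm is fixed by the school he attended at allocation.

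**2. The plan's own sample size**

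The inputs under Sample size calculation are SD 25.25, difference 12, 80% power and 95% confidence (two-sided 0.05 under Statistical analysis). The formula in Figure 2 is not shown, so the standard one is used.

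- Normal approximation: n = 2 × (25.25 × (1.960 + 0.842) / 12)² = 69.5, so 70 per group; 70 / 0.70 = 100.
- t-test version: 71 per group; 71 / 0.70 = 101.4, so 102.

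The 102 reproduces, and the 30% is a loss allowance of the form n / (1 − loss).

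**3. How many students could be affected**

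102 × 0.30 = 30.6, about 31 per arm; 204 × 0.30 = 61.2, about 61 in all. This allowance covers dropout of every kind, including plain non-response, which the exclusion rule does not mention. It is an upper planning figure for the students caught by the rule, not a forecast.

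**4. What the documents allow one to say about bias**

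Let p be the share excluded in an arm and D the amount by which the excluded students would have scored below those retained. The retained mean exceeds the full-arm mean by p × D, so

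bias in the difference (intervention minus control) = p_I × D_I − p_C × D_C.

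The document gives none of these four quantities. The values below are assumptions chosen to show the range.

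| p_I | D_I | p_C | D_C | Bias (points) | Share of the 12-point target |
|---|---|---|---|---|---|
| 0.30 | 12 | 0.15 | 12 | 3.6 − 1.8 = +1.8 | 15% |
| 0.15 | 12 | 0.30 | 12 | 1.8 − 3.6 = −1.8 | −15% |
| 0.30 | 12 | 0.30 | 12 | 0 | 0 |
| 0.30 | 12 | 0.30 | 0 | +3.6 | 30% |
| 0.10 | 12 | 0.10 | 0 | +1.2 | 10% |

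The sign changes with the arm that loses more, and the size depends wholly on the assumed values.

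**5. Power, ignoring clustering by school**

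With all 102 per group analysed, power is 92.4%. With about 71 per group left after the full 30% loss, it is 81%.

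**The case against.** The strongest reply is that the statistical section states ITT explicitly, so an analyst would follow it and treat the exclusion list as loose wording. That may well happen, but the list speaks of the analysis in terms, and nothing says which section governs. An analysis plan that is not shown could fill a gap; it would not remove two opposing statements from this article.

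Other parts of the opposing case stand and limit the point:

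- **Direction.** A reader might infer that the excluded intervention students would be the least engaged, so that the rule favours the intervention. The document does not support this. Its only remark on differential retention concerns the control arm, and higher control loss with similar selection would push the bias the other way.
- **Extent.** A reader might infer that the rule would remove 30% of students. The 30% is a general dropout allowance, and non-response alone does not trigger the exclusion.
- **Precision.** The planned number already absorbs a 30% loss at about 81% power (unclustered), so the stated power does not depend on this wording.
- **Consent.** Under Withdrawal option, students and parents may leave at any time. Removing data when consent to their use is withdrawn does not breach ITT. The defect lies in excluding students who merely become unwilling to continue, or who move.

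**Conclusion.** The point holds as a contradiction over the primary analysis population. It rests on two explicit statements, not on an omission, and needs no numerical assumption. Applying the exclusion rule would break the randomised comparison and discard usable scores.

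Neither the direction nor the size of the resulting bias can be stated. Under the assumed values above it runs from −1.8 to +3.6 points against a 12-point target, and it is zero if loss and selection are equal in the two arms. At most about 31 students per arm are affected if dropout stays within the plan's allowance. The sample size is not in question. The wording should be corrected before any data are analysed; the Trial status section describes the trial as still being planned.

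**What to change.** 1. Under Exclusion criteria, delete the exclusion from the analysis, or state that it defines a per-protocol or sensitivity set only.
2. Under Statistical analysis, state that the primary ITT analysis places every student in the arm to which his original school was allocated and uses all scores he provided, unless consent to use the data is withdrawn.
3. Under Data collection, state that the online questionnaire link continues to be sent to students who move or stop the sessions but still consent to follow-up.
4. State that the multilevel model or GEE already named in the statistical section will use all available visits, so that a student with a 3-month score but no 6-month score still contributes.

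This concerns who is analysed and followed up. It sets no rule on when a student stops the sessions. Keeping a student in the set does not supply scores he never gave, and the handling of those can stay with the analysis plan.

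The cost is a change of wording and a few extra questionnaire links. The planned 102 per group is unchanged.

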#### Intervention

Our planned intervention will utilize the Iranian social media platforms, Rubika and Eitaa, to disseminate the educational content of The Guide. The first author, acting as the primary facilitator, will conduct the program, which will be delivered through both synchronous and asynchronous formats. This blended approach allows for flexibility in learning while maintaining key engagement opportunities.

##### Facilitator and coordination

The first author will lead the educational program, organizing briefing sessions to ensure participants are well-informed about the program’s objectives, procedures, and expectations. These sessions will be conducted synchronously, allowing real-time interaction for better understanding and coordination.

##### Implementation details

The program will be structured around The Guide, with a thematic framework (outlined in Table 1) guiding the content. Methods will be in place to facilitate deep engagement, including real-time sessions and asynchronous materials for flexible access.

**Table 1 tab1:** Thematic framework of mental health literacy and methods of deepening and feedback.

	The subject of intervention	Deepening and feedback
1	Introduction: Mental health, mental disorders and brain functions	Question and Answer
2	The stigma Definition of stigma Stigma: Myths and realities of mental illness Which famous people lived with a mental illness?	Educational video Questions and Answers Stories
3	Information about specific mental illnesses What happens when the brain gets sick? Common mental illnesses Understanding common mental disorders in adolescents Sharing knowledge	Educational video Questions and Answers
4	Mental disorders of cognition and perception: psychotic disorders: Schizophrenia	Educational video Questions and Answers
5	Mental disorders of emotion and feeling: Mood disorders: Depression and bipolar disorder	Educational video Questions and Answers Stories
6	Mental disorder in signaling: Generalized anxiety disorder, social anxiety disorder and panic disorder	Educational video Questions and Answers
7	Other mental disorders with hyperarousal symptoms: Obsessive Compulsive Disorder and Post Traumatic Stress Disorder	Educational video Questions and Answers
8	Psychosomatic disorder: eating disorders Anorexia nervosa and bulimia nervosa	Educational video Questions and Answers
9	Behavioral disorders: ADHD, substance-related disorders, conduct disorder	Educational video Questions and Answers
10	Behaviors related to mental disorders: Suicide and self-harm	Educational video Questions and Answers Stories
11	Experiences of mental illness and the importance of family communication Seek help and find support	Question and Answer
12	Seek help and find support	Question and Answer
13	What if (future scenarios in case of certain symptoms)	Question and Answer
14	The importance of positive mental health	Educational video Questions and Answers
15	List of community mental health resources	Question and Answer

##### Duration and social media platforms

The intervention will span 1 month, consisting of 15 sessions. Each session will last approximately 30 min to 1 h, with 3–4 sessions delivered per week to ensure timely completion. The content will be regularly updated on Rubika and Eitaa, allowing participants to access both synchronous and asynchronous materials.

##### Incentives and participant engagement

Participants will be encouraged to actively engage through ongoing support, educational videos, and interactive Q&A sessions. Although the program is structured, participants will not have the flexibility to choose specific sessions based on preference, as all sessions are integral to the overall intervention. These strategies aim to maintain engagement throughout the study, with particular focus on improving retention, especially in the control group.

The educational content that the control participants receive at the end of the study will be provided in-person as a guide book rather than the online platform session content.

Please refer to Figure 1 for a visual representation of the intervention components, illustrating the topics covered and the methods employed for deepening and feedback.

### Data collection

In this randomized trial study, the statistical population consists of secondary school students from schools in Ramhormoz city. After coordinating with the schools and obtaining the phone numbers of the students, the link of the questionnaire that was created through Porsline website will be shared with them. The students will be asked to complete the study tool before, 3, and 6 months after the intervention.

### Primary outcome measure

#### Mental health literacy scale (MHLS)

This questionnaire was developed and validated by O’Connor in 2015. This scale has 35 items and 6 dimensions to measure the level of MHL. The Persian version of this questionnaire has 29 items that have been psychometrically evaluated by Nejatian et al. (2021), and it includes the following six sections:People’s ability to diagnose mental disorders: This feature consists of eight items (for example: Do you think personality disorder is considered other than mental illness). This feature is measured using a 4-point Likert scale (very unlikely, unlikely, likely, very likely) is measured with a score range of 8–32.Attitudes that promote appropriate help-seeking cognition or behavior: This trait includes 10 items (e.g.: If I have a mental disorder, I do not like to tell anyone). This trait is assessed using a 5-point Likert scale [(strongly disagree, disagree, neither agree nor disagree, agree, strongly agree) or (definitely willing, probably willing, neither willing nor unwilling, probably not willing, definitely not willing)] will be measured. Score range from 10 to 50.Awareness of self-healing: This feature includes two items (for example: if a person has a lot of difficulty managing his emotions, such as being anxious or depressed, how much do you think improving the quality of sleep would be useful for him?). This feature is measured using a 4-point Likert scale (not very useful, not useful, useful, very useful) with a score range of 2–8.Awareness of available professional help: This feature includes three items (e.g.: In your opinion, it is likely that cognitive behavioral therapy based on challenging negative thoughts and increasing beneficial behaviors). This feature is measured using a 4-point Likert scale (very unlikely, unlikely, likely, very likely) with a score range of 3–12.Awareness of where to look for information: This feature includes four items (e.g., I am sure that I can use the computer and telephone to look for information about mental disorders). This trait is measured using a 5-point Likert scale (Strongly Disagree, Disagree, Neither Agree nor Disagree, Agree, Strongly Agree) with a score range of 4–20.Awareness of risk factors and causes: this characteristic consists of two items (for example: in general, to what extent do you think men in Iran may experience anxiety disorders more than women). This feature is measured using a 4-point Likert scale (very unlikely, unlikely, likely, very likely) with a score range of 2–8.

A high score for each attribute indicates a higher literacy rate for each attribute. Also, the total score of MHLS is obtained from the sum of the scores of all features. The lowest score is 29 and the highest is 130. Higher scores indicate more favorable MHL status. Based on the reliability results, MacDonald’s omega coefficient and Cronbach’s alpha coefficient for all MHLS features were 0.797 and 0.789, respectively.

### Secondary outcome measures

#### Scale of attitude towards seeking professional psychological help

ATSPPH-SF is a 10-item scale used to assess ATSPPH on a 4-point Likert scale, ranging from 0 to 3. The total scores range from 0 to 30, where a higher total score indicates a more positive ATSPPH and is associated with lower levels of stigma against mental illness. This scale included two dimensions: (1) openness to seeking professional help for emotional problems (items 1, 3, 5, 6, 7) with item scores from zero (disagree) to three (agree) (2) value and need in seeking help professional (items 2, 4, 8, 9, 10) with reverse scoring of items (zero = agree and three = disagree).

### Statistical analysis

The statistical analysis of this study will be based on the intention-to-treat (ITT) principle, which includes all randomized participants regardless of their adherence to the intervention or their status at the end of the trial. The ITT analysis will preserve the balance of baseline characteristics achieved by randomization and reduce the risk of bias due to selective reporting or loss to follow-up (Hemming et al., 2020).

#### Potential confounds

Researchers anticipate several potential confounds that may influence the outcomes, such as:Pre-existing Mental Health Conditions: Variability in participants’ baseline mental health status may affect their response to the intervention.Socioeconomic Factors: Differences in socioeconomic status might influence participants’ access to mental health resources, potentially impacting outcomes.

The primary outcome of this study is the change in mental health literacy score (MHLS) from baseline to post-intervention and follow-up. The secondary outcome is the change in attitude towards seeking professional psychological help score from baseline to post-intervention and follow-up. Both outcomes will be measured using validated scales.

Demographic and baseline characteristics of the participants will be summarized using descriptive statistics, including mean, standard deviation, median, interquartile range, frequency, and percentage, as appropriate. The normality of the outcome variables will be assessed using graphical methods (histograms and Q-Q plots) and numerical tests (Shapiro–Wilk test). If the outcome variables are normally distributed, parametric tests will be employed; otherwise, non-parametric tests will be utilized.

Between-group differences in outcome variables at post-intervention and follow-up will be analyzed using analysis of covariance (ANCOVA), adjusting for baseline values and other potential confounders. Within-group changes in outcome variables from baseline to post-intervention and follow-up will be analyzed using paired t-tests or Wilcoxon signed-rank tests, depending on the normality assumption. Effect sizes and 95% confidence intervals will be reported for all comparisons.

We will employ techniques such as multilevel modeling (also known as hierarchical linear modeling) or generalized estimating equations (GEE) to model dependencies among observations within the same cluster. The level of significance for all statistical tests will be set at 0.05 (two-sided). All analyses will be conducted using SPSS software version 26.0.

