**Results:**

We anticipate a significant improvement in the mental health literacy score of the intervention group compared to the control group at post-intervention and both follow-ups. Additionally, we expect a substantial enhancement in the attitude towards seeking professional psychological help score for the intervention group compared to the control group at post-intervention and 6-month follow-up, though not at the 3-month follow-up.

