### Sample size calculation

The main goal of this study is to determine the effect of education on the average score of mental health literacy in two intervention and control groups, which will be analyzed as the difference between the two averages. Since the minimum and maximum score of mental health literacy is between 29 and 130, therefore, the standard deviation of 25.25 points was considered and the number of samples in each group was determined in such a way that with 95% confidence and 80% test power, if the difference between the two averages A score greater than 12 is statistically significant. From the following formulas, the number of participants in each group was stated (Figure 2).

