### Primary outcome: mental health literacy (MHL)

In accordance with our assumptions, the intervention group is expected to display statistically significant advancements in MHL scores compared to the control group at each assessment juncture (*p* < 0.05). This suggests an anticipated sustained enhancement in MHL among those exposed to the intervention.

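### The primary outcome is compared at two or three post-baseline visits, each at two-sided 0.05, and no visit or testing order decides the trial

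*Protocol article*

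**What the plan says.** All references are to the protocol article.

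- **Primary outcome** (Statistical analysis, under Potential confounds): "The primary outcome of this study is the change in mental health literacy score (MHLS) from baseline to post-intervention and follow-up". The definition spans several assessments and ranks none of them.
- **Test** (same section): "Between-group differences in outcome variables at post-intervention and follow-up will be analyzed using analysis of covariance (ANCOVA"), adjusted for baseline and other potential confounders.
- **Significance level** (same section): "The level of significance for all statistical tests will be set at 0.05 (two-sided"). No order of testing or adjustment accompanies it.
- **Sample size** (Sample size calculation): the aim is a comparison of mean MHLS between two groups, "which will be analyzed as the difference between the two averages". It uses a difference of 12 points, SD 25.25, 95% confidence and 80% power, and names no visit.
- **Number of visits**: Data collection gives two post-baseline assessments: "The students will be asked to complete the study tool before, 3, and 6 months after the intervention". The Methods paragraph of the abstract agrees. The Results paragraph of the abstract expects an MHLS benefit "compared to the control group at post-intervention and both follow-ups", which makes three, and the anticipated results for the secondary outcome also list post-intervention, 3 months and 6 months.
- **Expected result** (Primary outcome: mental health literacy): the intervention group is expected to show "statistically significant advancements in MHL scores compared to the control group at each assessment juncture".

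**The concern.** Taken together, these statements create two or three primary between-arm tests, each at the full 0.05. The sample size calculation covers one. Nothing says which result makes the trial positive, so the stated 5% error and 80% power attach to no defined test.

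The article also reads its outcomes visit by visit. For help-seeking attitudes, the abstract expects benefit at 6 months but not at 3 months, and the later results section expects the reverse. In a trial run without blinding, an open choice of visit leaves room to rest the conclusion on whichever one turns out favourable.

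**Working it through.** **1. Reproducing the plan's sample size.** Inputs from Sample size calculation: difference 12, SD 25.25 (equal to (130 − 29)/4), two-sided 0.05, power 80%, dropout 30%.

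n per arm = 2 × [25.25 × (1.960 + 0.842)/12]² = 69.5, so 70. Dividing by 0.70 gives 100. The t-test version gives 71, and 71/0.70 = 101.4, so 102. The stated 102 per group is therefore a calculation for **one** test on about 70 evaluable students per arm. With 70 per arm, the power of that one test is 80.3%.

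**2. Any-visit and all-visit rules.** Let k be the number of visits, ρ the correlation between the visit-specific test statistics (not in the article, so an assumption), and c = 1.96. The expected test statistic per visit, without baseline adjustment, is μ = 12/(25.25 × √(2/70)) = 2.81. With equal correlations, φ and Φ the standard normal density and distribution function, and x the shared normal factor:

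- Error if any visit counts = 1 − ∫ φ(x) [Φ((c − √ρ·x)/√(1−ρ)) − Φ((−c − √ρ·x)/√(1−ρ))]^k dx
- Power if all visits must succeed = ∫ φ(x) [1 − Φ((c − μ − √ρ·x)/√(1−ρ))]^k dx, with a true difference of 12 at every visit

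| ρ (assumed) | Any-visit error, 2 visits | Any-visit error, 3 visits | All-visit power, 2 visits | All-visit power, 3 visits |
|---|---|---|---|---|
| 0 | 9.75% | 14.3% | 64% | 52% |
| 0.5 | 9.1% | 12.5% | 69% | 62% |
| 0.7 | 8.4% | 10.9% | 72% | 66% |
| 0.8 | 7.8% | 9.8% | 73% | 69% |
| 0.9 | 7.0% | 8.4% | 75% | 73% |

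Simulation with 1,000,000 draws at ρ = 0.5 and 0.7 agrees. If single-visit power is set at exactly 80%, the three-visit figure at ρ = 0.5 is 61%.

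**3. Effect of the planned baseline adjustment.** ANCOVA with baseline–outcome correlation r (also an assumption) raises the expected statistic to μ/√(1−r²) and changes the between-visit correlation to (ρ − r²)/(1 − r²). With raw ρ of 0.5–0.8 and 70 per arm:

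| r (assumed) | All-visit power, 2 visits | All-visit power, 3 visits |
|---|---|---|
| 0 | 69–73% | 62–69% |
| 0.3 | 74–77% | 66–73% |
| 0.5 | 82–85% | 76–82% |
| 0.6 | 89–90% | 84–88% |

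At r = 0.5, for example, the expected statistic is 2.81/√0.75 = 3.25 and the adjusted correlation is 0.33–0.73. The any-visit error does not improve. It becomes 8.2–9.5% for two visits and 10.6–13.5% for three.

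**4. What a single primary visit does.** Error returns to 5%, and power is 80.3% on the plan's own basis with 102 per group. For comparison, splitting alpha equally (Bonferroni) would need 85 evaluable per arm for two visits (85/0.70, so 122) or 93 for three (93/0.70, so 133).

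**The case against.** The strongest reply is that the article contains neither an any-visit nor an all-visit rule, that a separate analysis plan may name the primary visit, and that a journal article need not set out multiplicity handling. The first part is correct, so every figure above is conditional on a rule the article does not state. The rest does not remove the point. The article does fix the primary outcome over several visits, the comparison at those visits and the level for every test. An analysis plan that chose one visit would have to narrow what is written here. The sentence on multilevel models or GEE deals with dependence within clusters and does not define one overall test across visits.

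A reader might infer that the article demands significance "compared to the control group at each assessment juncture". It does not. That phrase stands in a section that describes its contents as anticipated and based on assumptions, so it is a prediction and not a decision rule.

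A reader might also infer that power certainly falls below 80% if all visits must succeed. That does not hold either. The 61–73% range ignores the planned baseline adjustment, which could restore 80% or more (step 3). If all 102 per arm were retained, the unadjusted figures would be about 87–89% for two visits and 83–87% for three. Randomising schools pushes the other way, but that is a separate matter.

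Finally, testing the secondary outcome at 0.05 does not by itself inflate the error of the primary claim, so no separate complaint is made about it.

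**Conclusion.** The point stands in this form: the primary outcome has several time points at full alpha, no deciding visit or order, an inconsistent number of assessments, and a sample size for a single test.

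The firmer consequence is the error rate. Under an any-visit reading it is about 8–9% (two visits) or 10–12.5% (three) at an assumed correlation of 0.5–0.8, and about 7–14% over correlations from 0 to 0.9, against a nominal 5%.

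The power consequence is weaker. Under an all-visit reading the stated 80% no longer describes the test, but whether actual power is below or above 80% depends on the baseline correlation, retention and clustering, none of which the article quantifies for this purpose beyond the 30% dropout. The matter should be corrected. It does not call the design into question.

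**What to change.** 1. Reconcile the number of post-baseline assessments. State whether there is a separate post-intervention measurement in addition to 3 and 6 months, and make the abstract, Data collection, Statistical analysis and anticipated results agree.
2. Name one visit as the single primary between-arm MHLS comparison, at two-sided 0.05, using the baseline-adjusted analysis that accounts for school clustering. The article gives no ground for preferring a particular visit, so the sponsor should choose the one that matches the main claim.
3. Test MHLS at the remaining visit or visits in a pre-stated fixed order, each at 0.05, stopping at the first failure.
4. Keep ATSPPH-SF as secondary, either later in that order or reported as supportive.
5. Settle all of this before any outcome data are compared by arm. The trial is open, so there is no unblinding step to serve as the deadline.

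**Cost:** wording only. Later tests lose confirmatory status if an earlier one fails. The 102 per group is unaffected by this change; whether it suffices with schools as the randomised units is a separate question.
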